### Economic evaluation

The economic evaluation will be based on a cost-effectiveness analysis to determine whether the multifaceted care intervention is more cost-effective than usual care in reducing CAUTI amongst hospital inpatients. A healthcare provider perspective will be adopted. International guidelines for conducting economic evaluations, as recommended by Drummond et al.[45], and Husereau et al. [46] will be followed. Resource use will be identified using a short data collection instrument. Cost related data collected from usual care and intervention arms will include: materials used for catheterisation, proportion of patients receiving IDC, CAUTI rates, LoS for patients diagnosed with CAUTI, and CAUTI treatment expenses (e.g. antibiotics).

The measure of effect will be based on the change in the rate of CAUTI between the usual care and intervention groups. If the expected intervention benefit is demonstrated in the trial, the measure of effect will be the cases of CAUTI avoided due to the intervention. The economic analysis will identify the cost to avoid an additional case of CAUTI. The reportable outcomes will be average cost-effectiveness and incremental cost-effectiveness ratios. A sensitivity analysis will be conducted to explore the robustness of the results to the uncertainty around parameters used in the model. The results will be interpreted in a broader decision making framework that includes acceptability and sustainability of the intervention. The economic sustainability of the intervention will be based on the cost and effect of delivering the intervention in a wider setting. The analysis will also report the resources required to implement the intervention in other localities. This information is relevant to policy makers because it reflects the resources required by other Health Districts to implement the intervention.

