Studies investigating use of IDCs and CAUTI have been lacking in the Australian context [29, 30]. Extant literature includes hospital-based rates of IDC usage and/or rates of CAUTI, with some discussion of documentation, appropriate indications for IDC, and staff knowledge. Wynne et al. (2014) [29] found a point prevalence of 12.4% of patients with IDC in situ, in a tertiary teaching hospital in Melbourne. This included an acute inpatient facility and a sub-acute aged care and rehabilitation service. Wynne et al.’s study did not report on the days IDC in situ or prevalence of CAUTI, and a differentiation between short-term and long-term IDC usage was not made. So et al. (2014) conducted a chart audit in a hospital in Sydney, finding catheter utilisation of 11%. A study of staff and patient knowledge of IDC usage in two general medical wards in a Melbourne hospital found that the mean time an IDC was in situ was 5.8 days, and that a physician’s awareness of IDC presence was significantly associated with a shorter time IDC in situ [31]. Giles et al. (2015), in a pilot study, found the prevalence of IDCs in two wards in an Australian hospital (urology ward = 25%; orthopaedic ward = 31%), and rate of CAUTI = 2.2% [32]. Giles et al. then went on to describe the development and pilot of a bundled approach to target IDC utilization and CAUTI, however results of the intervention were not reported. A large point prevalence study in six Australian hospitals by Gardner et al. (2014) found a CAUTI prevalence of 0.9%, and urinary catheter prevalence of 26.3% (88.7% of these being IDCs) [33].

The foregoing studies highlight a gap in knowledge in the Australian healthcare context, in that there have been no studies investigating the effects of an intervention on reducing IDC utilisation and CAUTI rates in an acute care setting.

A multifaceted evidence-based intervention was piloted in two wards in an acute care hospital in the Hunter New England Local Health District, leading to a 50% reduction in IDC insertions, significantly reduced IDC duration and number of patients treated for CAUTI [34].

Building from the positive results from the aforementioned pilot, the present study aims to implement and evaluate an intervention across four acute care hospitals in NSW, Australia. To control for secular trends, implementation of the intervention will be phased across the hospitals.

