### Statistical analysis – point prevalence data

Statistical analysis will be undertaken to determine differences in the prevalence of IDCs between Health District 1 (post) and Health District 2 (no intervention). A mixed methods analysis will compare pre and post data within the groups, across the time frame. Within group data will be stratified according to wards to allow for variation in the case mix of patients between wards. If differences in patient demographics are detected at baseline these will be controlled for in the between group analyses. Data linkage will be used to determine LoS and CAUTI rates for patients at each time point.

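### The economic evaluation's CAUTI effect rests on patients present at point prevalence surveys (about 5–19 cases per district per survey), and its cases-avoided measure depends on an undefined demonstrated benefit

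*Protocol article*

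**What the plan says.** All references are to the Protocol article.

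- **Source of CAUTI and stay data.** Statistical analysis – point prevalence data: "Data linkage will be used to determine LoS and CAUTI rates for patients at each time point". Table 2 (Data collection) sets these time points at baseline, 4 months and 9 months, and staff visit every adult inpatient bed. The Table 2 row is labelled as incidence of CAUTI and lists the infection control database among its sources.
- **Effect measure.** Economic evaluation: "The measure of effect will be based on the change in the rate of CAUTI between the usual care and intervention groups". The next sentence begins: "If the expected intervention benefit is demonstrated in the trial, the measure of effect will be the cases of CAUTI avoided". It does not say what counts as demonstrated, on which outcome, or what replaces the measure otherwise.
- **Reporting.** "The reportable outcomes will be average cost-effectiveness and incremental cost-effectiveness ratios". No condition is attached. Also: "A sensitivity analysis will be conducted to explore the robustness of the results to the uncertainty around parameters used in the model".
- **Cost inputs.** These include "LoS for patients diagnosed with CAUTI".
- **Sample size.** The calculation concerns catheter use only (15% to 9%). CAUTI is not powered.

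**The concern.** The economic result is a cost per CAUTI avoided, so its denominator is a difference in CAUTI. Three features of the text weaken that difference.

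1. A bed census on a few occasions finds very few infections.
2. Patients in bed on a given day are sampled in proportion to their stay. Their CAUTI rate and length of stay are therefore not those of admissions, which is what a count of cases avoided and a bed-day cost need.
3. Tying cases avoided to a favourable trial result, without defining that result, leaves room for an effect estimate used only when it looks good.

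The section presents its results as relevant to policy makers in other districts. A ratio driven by chance in a handful of cases would serve them badly.

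**Working it through.** **The plan's own figure.** 15% versus 9%, two-sided alpha 0.05, power 0.80, gives 460 per group uncorrected and 493 with continuity correction. The stated 500 per district is reproduced. It says nothing about CAUTI.

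**Inputs for CAUTI.**
- Patients per survey: 610 (District 1) and 860 (District 2), from the Power section. Table 1 gives 620 and 867.
- CAUTI proportion, low: the cited six-hospital survey "found a CAUTI prevalence of 0.9" per cent (Preventing CAUTI).
- CAUTI proportion, high: 2.2%, from the cited study of two wards; denominator not stated.
- Assumed effect: a 40% fall, borrowed from the catheter-use calculation.

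**Expected cases per survey at usual-care rates** (patients × proportion):

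| | 0.9% | 2.2% |
|---|---|---|
| District 1 (610) | 5.5 | 13.4 |
| District 2 (860) | 7.7 | 18.9 |

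With 867 beds the top value is 19.1. Two pooled surveys double these: 11.0–26.8 in District 1 and 15.5–37.8 in District 2. An effective intervention lowers them. If 2.2% applies only to catheterised patients, the count is about 2–4 per survey.

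**Power for a 40% fall**, intervention 610 versus control 860, Fisher's exact test, two-sided 0.05, no clustering allowance:

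| | 0.9% | 2.2% |
|---|---|---|
| One survey | 8% | 20% |
| Two pooled | 16% | 39% |

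A z-test approximation for one survey gives 11% and 23%. About 8,700 and 3,500 patients per group would be needed for 80% power.

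**Precision of the risk difference**, one survey. Half-width = 1.96 × √[q(1−q)/610 + p(1−p)/860], with q = 0.6p:
- p = 0.9%: half-width 0.86 points, true difference 0.36 points.
- p = 2.2%: half-width 1.33 points, true difference 0.88 points.

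An interval centred on the true effect includes zero in both cases.

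**Length bias.** The mean stay in a bed census is the admission mean × (1 + CV²). The document gives neither the mean nor the CV, so the bias cannot be sized. As illustration only: the Background cites 4 added days for hospital UTI. On an assumed stay of 5 to 8 days, affected patients would be over-represented by (5+4)/5 = 1.8 to (8+4)/8 = 1.5 times.

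**Selection, by reading of the condition** (simulation, one survey, 40% fall; ratio of the mean selected difference to the true difference):
- Significance on CAUTI (pooled z-test): 3.0 at 0.9%, 2.0 at 2.2%.
- Favourable direction on CAUTI only: 1.44 at 0.9%, 1.15 at 2.2%.
- Benefit on catheter use: power for 15% versus 9% at 610 versus 860 is about 94%, so the condition would nearly always be met and selection on CAUTI is much weaker.

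**The case against.** **The ratio is not written as conditional.** A reader might infer that the cost-effectiveness result appears only when significant. The text does not say so: the change in CAUTI rate is set unconditionally, and the ratios and a sensitivity analysis are listed without a condition. This stands. Only the cases-avoided expression is conditional, and an exaggeration of 2–3 times needs one particular reading.

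**Total stay as the saving per case is an inference.** The section lists stay among patients with CAUTI as data collected. It does not say the whole stay is costed, and the Background speaks of additional days. This stands, so no upward bias in savings can be asserted.

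**The survey need not limit ascertainment.** Linkage could capture CAUTI over the whole admission, and the infection control database could cover the facility. The text fixes no window, so counts could exceed those above. But the analysis section names patients at each time point, and linking those patients to their full admissions leaves the length-biased sample unchanged.

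**The rates are borrowed.** The 0.9% is a prevalence elsewhere and the 2.2% comes from two wards. This stands as a limit on precision. It also means the gain in events from whole-month counting cannot be calculated: treating 0.9% as a per-admission incidence would confuse two quantities.

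**Length bias affects both groups.** True, so a relative effect is less affected. Absolute cases avoided and bed-day costs, which form the ratio, remain exposed.

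**A sensitivity analysis is planned.** It can display the uncertainty but cannot supply events.

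**Conclusion.** The point holds in limited form. CAUTI and stay are tied to patients found at point prevalence surveys while the outcome is labelled incidence. At the cited rates this means about 5–19 cases per district per survey, with power of about 8–20% for an assumed 40% fall, or 16–39% if two surveys can be pooled, before clustering. The ratio's denominator will be very imprecise and its absolute inputs come from a length-biased sample of unknown bias. The conditional wording is a defect because it is undefined and a decision analysis does not need it. The document does not establish that the reported effect is selected. This concerns a secondary aim; it should be corrected but does not touch the primary comparison of catheter use.

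**What to change.** (a) Take CAUTI counts from the infection control database, already a Table 2 source, over whole pre- and post-implementation months in both districts. Express them per 1,000 occupied bed-days and compare the change between districts. The article names no model for this comparison, so it must be specified.

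(b) Base the bed-day cost on the excess stay attributable to CAUTI, with length of stay from all discharges in those months. Days after onset are not a substitute, since they include days the patient would have stayed anyway.

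(c) Delete the condition on demonstrated benefit, and report cases avoided and the incremental ratio with full uncertainty whatever the result.

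Cost: a longer extract from systems already in use, and revised wording. The comparison then also relies on any difference between districts in database surveillance being stable over time. That needs stating, because the districts use different record systems (paper and electronic).

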## Discussion

A review of the literature highlighted a lack of interventional studies aiming to reduce IDC use or CAUTI rates in the Australian context. Internationally, there is a sparsity of studies using a control design in CAUTI intervention evaluations.

This study will add to the evidence-base through enhancing understanding of interventions to reduce CAUTI, using a control design to reduce secular effects.

Using the TIDieR framework, implementation strategies have been explicitly outlined, enabling easier replication of the intervention and implementation strategies. The use of a mixed methods approach will provide a platform to explore in-depth the existing barriers and enablers related to implementing practice change.

Ultimately, this study will improve patient safety through implementation and a robust evaluation of clinical practice and practice change.

## Abbreviations

AHRQ: Agency for Healthcare Research and Quality
CAUTI: Catheter-associated urinary tract infection
CEC: Clinical Excellence Commission
CUSP: Comprehensive Unit-based Safety Program
HAI: Healthcare-associated infection
IDC: Indwelling urinary catheter
LoS: Length of stay
TIDieR: Template for Intervention Description and Replication
UTI: Urinary tract infection.
